#### Power and sample size calculation

The estimation of the number of individuals needed in the randomized controlled trial is based on power calculations relying on the net difference of 0.6 mmol/l in the change of 2-h plasma glucose during the first 12 months of follow-up between the intensive lifestyle intervention group and the control group in the Finnish Diabetes Prevention Study [1]. Due to the real-life community-based approach in the StopDia study, we realistically anticipate achieving about 0.3 mmol/l net difference in the change of 2-h plasma glucose during the 12-month follow-up between the intervention group and the control group. We estimate that a minimum number of participants required to detect an effect size of at least 0.2 mmol/l in the change of 2-h plasma glucose concentration with a power of 80% (*p* = 0.05, allowing for a 10% loss to follow-up or missing data) is 1000 participants in each group.

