#### Examination visits and randomization

Individuals identified to be eligible by the StopDia Digital Screening Tool are automatically invited to participate in the randomized controlled trial. On the StopDia webpages, an individual who is willing to participate is given instructions on how to contact a nurse in a local health care center for examination visits.

At the first examination visit, the participant signs an informed consent, and the nurse measures body weight, body height, waist circumference, and blood pressure using calibrated devices, makes a referral to the laboratory measurements, and gives a blood sampling kit and tubes to the participant for the laboratory measurements. The sampling kit and the tubes are identified with numerical identification codes. After the first examination visit, the participant receives a personal link by email to a web-based StopDia Digital Questionnaire developed using the LimeSurvey platform (LimeSurvey GmbH, Hamburg, Germany). The participant is instructed to complete the questionnaire within two weeks.

The second examination visit is carried out in the laboratory of the local health care center. The participant is instructed to fast for 12 h, avoid strenuous physical activity, abstain from drinking alcohol for 24 h, and avoid smoking in the morning before the visit. Trained laboratory nurses take fasting blood samples for routine laboratory tests, explained in detail in Assessments, and blood samples during the 2-h OGTTs. These blood samples are stored and analysed at local clinical laboratories. Additional blood samples for research purposes, taken with a sampling kit, are frozen and transported to the laboratory of the StopDia research group at the University of Eastern Finland.

The participants who meet the inclusion criteria and have no exclusion criteria according to the StopDia Digital Screening Tool, have filled out the StopDia Digital Questionnaire, have given blood samples, and have no type 2 diabetes according to the results of the 2-h OGTT are randomly assigned into one of the three study groups (digital lifestyle intervention, digital and face-to-face group lifestyle intervention, control) with 1:1:1 allocation using a computerized randomization system. Individuals whose 2-h OGTT indicates the diagnosis of type 2 diabetes are directed to diabetes care following the normal principles of the provinces.

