#### Primary and secondary outcomes

The primary and secondary outcomes of the randomized controlled trial are changes in the corresponding variables during the 1-year follow-up listed in Table 4. Each of them are described in more detail in the following paragraphs.

**Table 4 Tab4:** The primary and secondary outcomes of the randomized controlled trial

Primary outcomes	Secondary outcomes (in more detail below and in ClinicalTials.gov. Identifier: NCT03156478)
Body weight	Waist circumference
Fasting plasma glucose	Serum insulin and plasma lipids
Two-hour plasma glucose from OGTT	Systolic and diastolic blood pressure
Dietary score	Sedentary behavior
Total physical activity	Psychosocial factors and mental wellbeing Use of health and social care and associated costs

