#### Statistical analyses

The statistical analyses will be performed following the CONSORT 2010 statement guidelines for randomized controlled trials. The effects of the intervention on the primary and secondary outcomes during follow-up are analysed using the intention-to-treat principle. Linear mixed effects models adjusted for relevant confounding factors are used to analyse the effects of the interventions on the outcomes. Appropriate correction methods are used to reduce the likelihood of false positive findings in the statistical analyses. Differences in variables between the groups and associations and interactions between variables with *p*-values of < 0.05 are considered statistically significant. Most of the statistical analyses are performed using the IBM SPSS Statistics® software (IBM Corp., Armonk, NY, USA), but the SAS and R software may also be used.

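### The stated 80% power for 0.2 mmol/l in 2-h glucose makes no allowance for the multiplicity correction that the protocol itself promises

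*Protocol article*

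**What the plan says.** Under Power and sample size calculation, the protocol article takes a 0.6 mmol/l difference in 2-h glucose change from an earlier Finnish prevention trial and scales it down: "we realistically anticipate achieving about 0.3 mmol/l net difference in the change of 2-h plasma glucose". It then sizes the trial for a smaller difference still, an "effect size of at least 0.2 mmol/l in the change of 2-h plasma glucose concentration with a power of 80" per cent, at p = 0.05 and with an allowance of 10% for loss or missing data. The result, 1000 in each group, is presented as the smallest number that will do. No SD is given. The comparison is described in the singular, one intervention group against control. Loss is the only allowance listed.

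Other sections describe a wider testing plan:

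- Participants "are randomly assigned into one of the three study groups" in equal proportions (Examination visits and randomization). Aims of the study sets two comparisons: the digital intervention, and the digital plus group intervention, each against routine care.
- Table 4 lists five primary outcomes: body weight, fasting glucose, "Two-hour plasma glucose from OGTT", dietary score and total physical activity. None is ranked above the others.
- Statistical analyses commits to correction: "Appropriate correction methods are used to reduce the likelihood of false positive findings in the statistical analyses". It names neither the method nor the family of tests, and also gives 0.05 as the significance threshold.

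**The concern.** If 1000 per group is the smallest number giving 80% power at 0.05, there is no slack. Any correction that lowers the threshold for 2-h glucose must leave less than 80% power at 0.2 mmol/l. On a plain reading, then, the power section and the analysis section describe two different tests of the same outcome.

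The consequence lies in how a null result is read. Someone told that the trial had 80% power against 0.2 mmol/l may take a null on 2-h glucose as good evidence against an effect of that size. This matters most for the digital-only arm, where a small effect is plausible and a null could count against a scalable intervention.

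**Working it through.** **Inputs from the protocol article.** Difference 0.2 mmol/l; power 80%; p = 0.05; 1000 per group; 10% loss; three groups at 1:1:1; five primary outcomes; two intervention-control contrasts.

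**Assumptions.** A two-sided test, an unadjusted comparison of mean change, the normal approximation, and 1000 per group being exactly the 80% requirement.

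**Step 1: the plan's own figure.** Without an SD, 1000 cannot be checked independently. It can only be inverted.

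- Evaluable per group: 1000 × (1 − 0.10) = 900.
- Implied SD of change: 0.2 × √(900/2) / (1.960 + 0.842) = 1.51 mmol/l.
- Standard error of the difference: 1.514 × √(2/900) = 0.0714 mmol/l.

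This shows consistency with an SD near 1.5. It does not confirm the figure, because the SD was chosen to fit.

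**Step 2: power at corrected thresholds.** Under these assumptions 0.2 mmol/l lies 1.960 + 0.842 = 2.802 standard errors from zero, whatever the SD. At 0.3 mmol/l the distance is 1.5 × 2.802 = 4.202. Power is Φ(distance − critical value). The difference detectable with 80% power is 0.0714 × (critical value + 0.842).

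| Correction | Two-sided alpha | Critical value | Power at 0.2 | Power at 0.3 | Detectable at 80% (mmol/l) |
|---|---|---|---|---|---|
| None | 0.05 | 1.960 | 80.0% | 98.8% | 0.200 |
| Two contrasts, Dunnett | about 0.027 | 2.212 | 72.2% | 97.7% | 0.218 |
| Two contrasts, Bonferroni | 0.025 | 2.241 | 71.2% | 97.5% | 0.220 |
| Five outcomes, Bonferroni | 0.01 | 2.576 | 58.9% | 94.8% | 0.244 |
| Ten tests (5 × 2), Bonferroni | 0.005 | 2.807 | 49.8% | 91.9% | 0.260 |

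The Dunnett row uses the correlation of 0.5 between two contrasts that share a control group of equal size.

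**Step 3: sensitivity to sidedness.** If the 0.05 is one-sided, the implied SD is 1.71. Power at 0.2 mmol/l is then 70%, 56% and 46% with Bonferroni for two, five and ten tests, and power at 0.3 mmol/l with ten tests is 88%.

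**Step 4: a fixed sequence.** If 2-h glucose were tested first, with the contrasts in a set order, the first contrast would keep 0.05 and its 80%. The second is tested only if the first succeeds. With both true effects at 0.2 mmol/l and correlation 0.5, the chance that both succeed is about 69%. The protocol article states no such order.

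**The case against.** The strongest reply is that no arithmetic error has been shown. The SD is back-solved on the premise of an uncorrected test, and the same formula would fit 1000 per group to a corrected one: 0.2 × √450 / (2.241 + 0.842) gives an SD of 1.38 at 0.025, and 0.2 × √450 / (2.807 + 0.842) gives 1.16 at 0.005. This stands as a limit on proof. However, the text gives 0.05, lists 10% loss as its only allowance and refers to one intervention group, so the uncorrected reading is the natural one.

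Second, the size of the loss depends on a correction that the article does not name. Method and family may properly be left to an analysis plan, and their absence is not the point here. A fixed sequence starting with 2-h glucose would protect the first contrast. Step-up or false-discovery methods can test at up to 0.05 when other outcomes are positive. Bonferroni over ten correlated tests is the severe end. All of this stands, and it is why the loss is given as a range.

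Third, the planned analysis is an adjusted mixed model. As an illustration, assume a baseline to follow-up correlation of 0.5 and adjustment for baseline. Residual variance is then 0.75 of the change-score variance, the distance becomes 2.802/√0.75 = 3.235, and power at 0.2 mmol/l is about 84% at 0.025 and 67% at 0.005. So adjustment could recover part of the loss, or all of it under the mildest correction. The article gives no such correlation, does not name the covariates, and claims no such gain in its power section.

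Fourth, the practical effect is limited, because 0.2 mmol/l already lies below the anticipated 0.3. That is correct, and it bears on severity.

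**Conclusion.** The point holds at moderate severity. As written, the 80% applies to 2-h glucose alone, in one contrast, before correction. It does not match a plan with five unranked primary outcomes, two contrasts and a promised correction. On the stated assumptions, power at 0.2 mmol/l is about 71–72% after correction for two contrasts, 59% for five outcomes and 50% at the severe end. The detectable difference rises from 0.20 to 0.22–0.26 mmol/l.

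A reader might go further and infer that the sample size was miscalculated, or that the trial is underpowered. The document supports neither. Without the SD, the figure of 1000 is neither confirmed nor refuted. Two-sided power at the anticipated 0.3 mmol/l stays at about 92–98% after correction. Nor can the 50% be treated as the trial's true power, since nothing in the article says that all ten tests form one Bonferroni family.

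**What to change.** Amend the power section in one of two ways.

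1. Say that the 80% is per contrast, for 2-h glucose alone and before multiplicity correction. Add the power at 0.2 and 0.3 mmol/l, or the detectable difference, at the alpha that will apply to 2-h glucose once the promised correction is made.
2. Name 2-h glucose as the single or first-tested primary outcome and put the two contrasts in order. Say that the 80% then holds for the first contrast only.

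In either case, give the SD of change that was used and say whether the test is two-sided. If baseline adjustment is relied on to recover power, state the assumed correlation.

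The cost is wording only, with no change to enrolment. The downside is a less favourable stated power at 0.2 mmol/l. The second option also commits the trial to a testing order that the article does not now contain.

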#### Statistical analyses

The statistical analyses will be performed following the CONSORT 2010 statement guidelines for randomized controlled trials. The effects of the intervention on the primary and secondary outcomes during follow-up are analysed using the intention-to-treat principle. Linear mixed effects models adjusted for relevant confounding factors are used to analyse the effects of the interventions on the outcomes. Appropriate correction methods are used to reduce the likelihood of false positive findings in the statistical analyses. Differences in variables between the groups and associations and interactions between variables with *p*-values of < 0.05 are considered statistically significant. Most of the statistical analyses are performed using the IBM SPSS Statistics® software (IBM Corp., Armonk, NY, USA), but the SAS and R software may also be used.

### Protocol for evaluating adoption, implementation, and maintenance

Adoption and implementation of the interventions will be evaluated with project logs, group facilitator logs, questionnaires, and interviews (setting level) as well as key informant interviews (societal level). Participation, experiences, and acceptability [64] dealing with the digital intervention and the face-to-face group intervention as well as experiences dealing with the StopDia study are assessed at the one-year follow-up questionnaire. We developed a seven-item questionnaire of acceptability based on the Theoretical Framework of Acceptability [64]. User data from the BitHabit application is used for measuring adherence, habit selection, and habit execution.

### Data management

Collected data will be stored in secure file servers at the University of Eastern Finland. The file servers are located in a locked and monitored server room. All data can be accessed only by users authorized by the principal investigator. Personal identification numbers will be only used to combine data from different sources, and access to these data will be restricted to within the University of Eastern Finland firewall. Coded data with identifiable information removed will be used for statistical analyses. At the end of the study, the data will be stored by the University of Eastern Finland or CSC - IT Center for Science.

### Ethical issues

The StopDia study was approved by Research Ethics Committee of Hospital District of Northern Savo (statement number: 467/2016). Written informed consent to participate in the study and the use of data from national health care registers is obtained from all participants. The study will be conducted according to the Responsible Conduct of Research by the Finnish Advisory Board on Research Integrity and the Declaration of Helsinki. The participants were permitted to have their usual care during the study. After the randomized controlled trial, the control group will be provided a possibility to start using the BitHabit application.

### Dissemination policy

We will publish study results in high-quality peer-reviewed international scientific journals and will prefer open-access journals. The publications will also be made openly available through parallel publishing in the publication archive of University of Eastern Finland. We will publish the most important findings in international scientific meetings as well as national scientific meetings and journals. Our articles in peer-reviewed international journals and our doctoral theses will be published on the website of University of Eastern Finland according to its publication policy. We will deliver almost all of our findings to the media through press releases, our webpages, and Twitter to disseminate them to health professionals, society decision makers, and the public.

## Discussion

The StopDia study is based on the convincing scientific evidence that type 2 diabetes and its comorbidities can be prevented by a healthy lifestyle. The reason for the need for additional research is that the attempts to translate scientific evidence into action in real-world health care have not led to permanent and cost-effective models for the prevention of type 2 diabetes. The StopDia study will complement previous research by 1) exploring how to improve reaching individuals at risk, 2) studying how to increase participation in and adherence to lifestyle intervention, 3) creating personalized intervention models, 4) evaluating the efficacy and cost-effectiveness of actions to improve lifestyle and prevent type 2 diabetes, and 5) promoting the adoption, implementation, and maintenance of the preventive actions that are fully intergrated in the Finnish routine health care. This will enable us to leverage our societal objective of developing a participatory, sustainable, and scalable prevention model for preventing type 2 diabetes that engages citizens, societal actors, and other stakeholders.

### Identification of individuals at increased risk of type 2 diabetes

One of the challenges in the prevention of type 2 diabetes has been how to reach individuals at increased risk of type 2 diabetes. Although knowledge on the risk factors and prevention of type 2 diabetes have increased in the society, there still are many people who do not recognize being at increased risk. To reach these individuals, we have developed a simple and non-invasive tool to reach these individuals. In the StopDia study, the FINDRISC is available in a digitalized format and to be completed at any time. However, providing the opportunity to screening individuals at increased risk is not enough. We need efficient communication strategies to increase the reach and uptake of risk identification, both within and outside health care services. In the StopDia study, we provide scientific evidence for the effects of the different recruitment approaches and emphasize reaching individuals from different population groups, including those with a lower socioeconomic position.

### Increasing motivation to participate in and adherence to lifestyle interventions

Ultimately, success to prevent type 2 diabetes at individual and societal level depends on the ability of the program to increase the adherence of participants to a healthy lifestyle. To achieve this, lifestyle interventions have largely focused on the motivation and capability of the participants. Although supporting autonomous motivation and self-regulation skills, such as goal setting and planning, have been proven to be effective in the short-term, the sustainability of lifestyle changes remains a challenge [65]. The theories of habit formation and automatisation offer potential solutions for sustainability. Based on habit theories, simple actions are easier to conduct and adopt if they are linked to a stable context and are repeated until they become automatised [28, 29]. Habit theories are suitable for digital interventions where simplicity and effortlessness are key factors. Habit theories were chosen for the StopDia BitHabit intervention tool. The advantages of the digital tools compared to traditional options are 1) the possibility to objectively measure adherence to the interventions, 2) the low cost of the interventions, and 3) that the interventions are not tied to time or place and are therefore flexible. On the other hand, there are still individuals who have no access to digital services or for whom such tools are not suitable. Especially for these individuals, face-to-face group lifestyle coaching might still be the most suitable and cost-effective choice for the prevention of type 2 diabetes.

### Creating personalized intervention models

Personalised approaches are needed to increase the commitment of individuals and the effectiveness of the interventions. The StopDia study enables us to explore interventions that could be suitable to different individuals and population groups and create a model to predict responses to the interventions. For the future, it will be of great importance that the model with its interventions can reach individuals from different cultural, ethnic, and socioeconomic backgrounds. Although the randomized controlled trial in the StopDia study could not include diverse populations with different needs, we are simultaneously adapting and piloting the model in two vulnerable population groups, immigrants and long-term unemployed people.

### Integrating the StopDia model to the society

To ensure the implementation of the StopDia model into real life we have closely collaborated with over 20 social and health care partners from the planning to realization of the study. Importantly, we are able to evaluate the effectiveness and cost-effectiveness of the actions to prevent type 2 diabetes as part of the routine health care in the real world environment. Combined with the co-creation of the actions, we are promoting adoption, implementation, and maintenance of the preventive actions as part of the routine health care.

Due to the limited economic resources, it is very important that the model created is effective and financially sustainable. Therefore, the direct link of the StopDia data with routine clinical and biochemical data, biobanks, and registries measuring the outcomes of the project is essential. Furthermore, the digital screening of individuals at increased risk, the collection of data on risk factors for type 2 diabetes, and intervention tools created in the StopDia study gather information that is not normally collected in the health and social care and could therefore be very useful in preventing type 2 diabetes in the future.

Sustainable and scalable models are needed to reach and identify individuals at increased risk of type 2 diabetes and to deliver personalized and effective lifestyle interventions. With the StopDia study we aim to answer these challenges in a scientific project that is fully integrated in the routine health care and thus allows the real-life assessment of cost-effectiveness of the intervention. Even though the StopDia study focuses on the prevention of type 2 diabetes, the same lifestyle goals and tools are effective in the prevention of other non-communicable diseases, such as cardiovascular diseases, dementia, osteoarthritis, and cancer. Therefore, the potential of the StopDia approach extends beyond the prevention of type 2 diabetes.

## Abbreviations

BMI: Body mass index
cm: Centimeter
DI_30_: Disposition index_30_
ecSI 2.0: The ecSatter Eating Competence Inventory 2.0
FINDRISC: The Finnish Diabetes Risk Score
HDL: High-density lipoprotein
kg: Kilograms
LDl: Low-density lipoprotein
Matsuda ISI: Matsuda index of insulin sensitivity
mmHg: Millimeter of mercury
mmol/l: Millimoles per litre
OGTT: Oral glucose tolerance test
PI: Principal investigator
RCT: Randomized controlled trial
RE-AIM: The Reach, Effectiveness, Adoption, Implementation, and Maintenance framework
StopDia: Stop Diabetes study
T2D: Type 2 diabetes
TFEQ-R18: The Three Factor Eating Questionnaire
WP: Work package
